Reminiscence therapy, as a potential psychological intervention to improve depressive symptoms in older adults, has an important therapeutic aspect of enhancing autobiographical memory and is often used interchangeably in the literature due to its similarity to the term “life review intervention” [24]. It enhances older people’s positive affect [25], cognitive functioning [26], social participation [27], quality of life, and ability to adapt to ageing [28] through the recall, narration, and reflection of past experiences. In addition to previous meta-analyses showing the significant effect of reminiscence-based interventions in improving psychological problems and enhancing well-being in older adults [29–31], there are also empirical studies showing that when researchers guided older adults through interventions for reminiscence at different stages of life, the older adults became more resistant to social stress, increased their ability to think and act for themselves, and finally, experienced completeness in the final stages of life [32–34]. However, in terms of the improvement of autobiographical memory, studies have shown that reminiscence therapy is not effective in improving it [35–37], possibly because reminiscence therapy is an inherent normative process of thinking about the past [38], rather than the practice and improvement of specific event details, which cannot significantly improve the effect of autobiographical memory.

Memory-specific training (MeST), as an intervention for improving autobiographical memory in some patients with mood disorders, has a good effect on patients’ difficulties in recalling personal events through the use of clues to recall words. Although MeST is simple and can be implemented singly, the effect is not good [39, 40]; thus, it can also be implemented together with traditional interventions such as reminiscence therapy as an adjunct therapy [40]. Consequently, there have been many studies combining these two therapies.

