Currently, reminiscence therapy combined with memory-specific training is mainly used in the psychological treatment of cancer patients in palliative care, and its effectiveness needs further validation, as randomized controlled trials of Life Review Therapy combined with Memory Specificity Training (LRT- MST) by Gitta Kleijn showed no significant differences between the two groups in terms of anxiety, depression, quality of life and autobiographical memory in cancer patients [41, 42]. However, other studies have shown that reminiscence therapy based on autobiographical memory training can be used in future studies to investigate available, cost-effective, low-intensity treatment options for patients experiencing mood disorders [43, 44]; thus, further investigation of this therapy is warranted.

Based on the national situation that depressed older people are increasing year by year in China, this study aims to implement a randomized controlled trial of reminiscence therapy combined with memory specificity training in a Chinese context to investigate whether this therapy can reduce rumination and improve depressive symptoms in older people and improve their psychological health by improving autobiographical memory. In this study, it is hypothesized that older people who participate in reminiscence therapy combined with memory specificity training will report improved autobiographical memory specificity, less rumination, and significantly lower levels of depressive symptoms at postintervention and follow-up time points than older adults receiving usual care and reminiscence therapy alone; we further hypothesize that these improvements will be maintained for 6 months after the intervention.

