### Sample size calculation

Based on a priori power analysis (G-power3.1.9.7) using a power of 0.90 and error probability of 0.05, with a reference to a literature effect size of 0.8 [46, 47], a sample size of 24 participants per group will be needed. Assuming a 10% drop out rate, a sample size of 78 participants will be initially targeted.

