### Statistical analysis

A database will be established using EpiData, and the data will be entered by two persons and analysed statistically using SPSS 26.0 software. The measurement data such as scale scores will be expressed as the mean ± standard deviation (x ± s). Count data such as general demographic data will be described by the frequency and percentage. The status of each scale score before and after the intervention within each group and the measurement data between multiple groups will be analysed by repeated-measures ANOVA and simple effects analysis if they are normal and have equal variance, and the statistics will be described by median and mean difference (MD). For measures with skewed distribution, median and quartiles will be used to describe the statistics, and Kruskal‒Wallis multiple comparisons will be used to compare the data between and within groups. Intention-to-treat will be used to process the data and P < 0.05 will be considered statistically significant.

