## Discussion

Depression in older people is a global public health problem. According to the World Health Organization, adults between the ages of 55 and 74 years are the people most affected by depression [59]. Late life depression (LLD) is a common disabling disorder, with a prevalence ranging from 9–45% [60], especially during the COVID-19 pandemic. Older people may be more vulnerable to the mental health effects of the pandemic and have a significantly increased risk of dementia, whether directly from the infection itself or indirectly from infection-preventive measures [61]. Cost-effective psychological interventions are urgently needed to improve depression in older adults.

Reduced autobiographical memory with increased overgeneral memory as a cognitive marker of depression is not only evident in individuals with a history of depression, but also predicts subsequent increases in symptoms [62]. Fortunately, studies have shown that this overgeneral memory is not a fixed feature of an individual’s memory style but can be modified [63]. In high-risk populations without a clinical diagnosis, the benefit of memory specificity training may be reflected in preventing further severity of symptoms [64], but its effectiveness alone is modest and short-lived [65].

Reminiscence therapy has received increasing attention as a psychotherapy that has been developed over a long period of time and has a more mature intervention model. It helps older adults gradually recall memories of past experiences and unresolved conflicts through many therapeutic aspects, alleviates negative emotions by integrating all past positive and negative experiences, fosters a sense of security, and helps support the intrinsic capacity of older adults to age healthily [28]. Therefore, we will implement a multicentre, single-blind, three-arm parallel group randomized controlled trial to investigate whether the combination of the two therapies can further confirm the role played by autobiographical memory in the overall improvement of depressive symptoms in older adults while promoting the emergence and implementation of more therapies targeting autobiographical memory.

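### One effect size of 0.8 and one power of 0.90 serve a hypothesis with two comparators; the contrast is not named, and 24 per group does not give 90% power at 0.8 for either pairwise comparison

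*Protocol article*

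**What the plan says.** The hypothesis at the end of the Background has two comparators. RT-MeST is expected to give "significantly lower levels of depressive symptoms at postintervention and follow-up time points than older adults receiving usual care and reminiscence therapy alone".

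Methods, Sample size calculation, gives one basis for the whole trial: "using a power of 0.90 and error probability of 0.05", and then "with a reference to a literature effect size of 0.8 [46, 47], a sample size of 24 participants per group will be needed". It adds 10% for dropout and arrives at 78 in total, which is 26 per arm. It does not say whether 0.8 describes RT-MeST versus usual care, RT-MeST versus RT, RT versus usual care, or an overall three-group test. It also does not say whether 0.8 is a standardised mean difference (d) or the ANOVA effect size f, or whether the test is one- or two-sided. Statistical analysis plans repeated-measures ANOVA with simple effects and states that "P < 0.05 will be considered statistically significant".

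Two parts of the rationale bear on the size of each contrast. The Background cites "previous meta-analyses showing the significant effect of reminiscence-based interventions in improving psychological problems", so RT is presented as effective in its own right. The Background also describes MeST given singly as having a poor effect, and the Discussion says of it, "but its effectiveness alone is modest and short-lived".

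**The concern.** RT-MeST versus RT is the only comparison that isolates what memory specificity training adds, because the two arms otherwise share the same sessions and content. It is a contrast between two active arms, so it would normally be expected to be smaller than a contrast with usual care. A single effect size and a single power figure, with no contrast attached, invite the reader to take 90% as covering both parts of the hypothesis.

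If it does not, a non-significant RT-MeST versus RT result could be reported as showing that MeST adds nothing when the trial had limited ability to detect a moderate addition.

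**Working it through.** **Inputs.** Power 0.90, alpha 0.05, effect size 0.8 and 24 per group come from Sample size calculation. The two comparators come from the Background. Assumptions made here: 0.8 is a standardised mean difference, the test is a two-sample t-test, and residents are independent.

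**1. Reproducing the plan's figure.** The normal approximation is n per group = 2(z₁₋α/₂ + z₀.₉₀)²/d².
- Two-sided: 2(1.960 + 1.282)²/0.64 = 32.8, so 33 (34 with the t distribution).
- One-sided: 2(1.645 + 1.282)²/0.64 = 26.8, so 27 (28 with the t distribution).
- One-way three-group ANOVA at 90% power: 8 per group if f = 0.8, 28 if f = 0.4, and 31 to 41 if the largest pairwise difference is 0.8 SD.

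None of these gives 24. A repeated-measures ANOVA between-group test can give 24, but only after converting 0.8 to another metric and adding a correlation that is not stated. With f = 0.4, for example, it takes a correlation of 0.7 with two measurements or 0.8 with five.

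**2. Power that 24 per group delivers.** The noncentrality is δ = d√(n/2) = d√12, with 46 degrees of freedom and a two-sided critical value of 2.013. At d = 0.8, δ = 2.77.

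| d | Power, two-sided | Power, one-sided |
|---|---|---|
| 0.8 | 77% | 86% |
| 0.6 | 53% | 66% |
| 0.4 | 27% | 39% |

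Power of 90% needs d of about 0.96 two-sided (0.86 one-sided). These figures apply to any pairwise contrast with 24 per arm, whichever comparator is used.

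**3. Can 0.8 describe both contrasts?** On one SD scale,

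(RT-MeST − usual care) = (RT-MeST − RT) + (RT − usual care).

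If both hypothesised contrasts equal 0.8, then RT − usual care = 0.8 − 0.8 = 0, which conflicts with the Background's statement that reminiscence works. So 0.8 fits at most one of them:
- If it is the usual-care contrast, RT-MeST versus RT is smaller than 0.8. An RT effect of 0.2 leaves 0.6 (53% power), and an RT effect of 0.4 leaves 0.4 (27%). The documents give no figure for RT, so this split is an assumption.
- If it is the RT-MeST versus RT contrast, the usual-care contrast is larger, and an n that is correct for 0.8 covers both. By step 2, however, 24 per group gives 77% at 0.8.

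**4. Precision.** The 95% CI half-width is t₀.₉₇₅,₄₆ × √(2/24) = 2.013 × 0.289 = 0.58 SD. An observed difference of zero would leave a benefit of half an SD inside the interval.

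**5. Sensitivity.** Baseline adjustment with an assumed correlation of 0.5 divides the SD by 1/√(1 − 0.25), in effect raising d by a factor of 1.155. Power becomes about 88% at 0.8 and 35% at 0.4.

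**6. Direction of the remaining error.** Expected completers are 26 × 0.9 = 23.4 per arm, slightly under 24. Randomization and blinding assigns whole nursing homes to interventions, one home per arm, so calculations that treat residents as independent are optimistic.

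**The case against.** The strongest reply is that the section never ties 0.8 to usual care and makes no power claim specific to RT-MeST versus RT. The two cited sources cannot be checked from the document. If 0.8 was meant for RT-MeST versus RT, the other contrast is larger and there is no mismatch between comparators. This stands. A reader might infer from step 3 that RT-MeST versus RT must be the uncovered comparison, but the text does not establish that.

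Nor does the rationale prove that the addition is small. The remark about a poor effect comes in a paragraph about improving autobiographical memory. The Discussion's remark concerns MeST alone, in a sentence about high-risk people without a clinical diagnosis. Neither gives the effect of MeST added to RT, and the Background proposes MeST as an adjunct because RT does not improve autobiographical memory. These remarks make 0.8 over active RT doubtful, not impossible, and any division of 0.8 between RT and MeST is assumed.

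It can also be said that the planned analysis uses repeated measurements, and that baseline or repeated-measures information could bring 24 close to 90% at 0.8. That is possible, but the section states neither a correlation nor the test. A three-group repeated-measures test is also not a pairwise contrast at a time point, and the hypothesis is worded in terms of pairwise superiority at post-intervention and follow-up.

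What the reply does not meet is that, on the inputs actually stated, 24 per group falls short of 90% at 0.8 whichever pairwise contrast was intended.

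**Conclusion.** The concern holds in a limited form. One effect size and one power figure serve a two-comparator hypothesis, with contrast, metric and test unstated. The two effects cannot be equal if RT is effective. With 24 per group, power at 0.8 is about 77% two-sided or 86% one-sided, against the stated 90%, which needs about 0.96. The 0.90 is therefore unsupported for RT-MeST versus RT and, on the same inputs, for RT-MeST versus usual care. It would be wrong to conclude that 90% stands for usual care and fails only for RT.

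The 77% rests on reading 0.8 as a standardised mean difference tested by a t-test at alpha 0.05 with independent residents. The 53% and 27% for RT-MeST versus RT rest further on assumed effects of 0.6 and 0.4 and illustrate a range; they do not measure an error in the document. All are optimistic under allocation of one home per arm.

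**What to change.** In Sample size calculation:
- State which contrast, effect metric, test and sidedness the 0.8 refers to.
- Restate the power at 24 per group for each hypothesised contrast: about 77% at 0.8 (two-sided t-test) and, for RT-MeST versus RT, a range such as 53% at 0.6 and 27% at 0.4. Label these effects as assumptions, and the figures as optimistic because they treat residents as independent while whole homes are assigned, one per arm.
- Withdraw the unqualified 0.90. If the calculation used a repeated-measures or baseline-adjusted model, give its correlation and the contrast it covers instead.

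In Statistical analysis, say that RT-MeST versus RT will be reported as an estimate with its 95% CI and that a non-significant difference will not be read as no added benefit of MeST.

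This takes a few sentences and no change to enrolment. The downside is a less favourable stated power.

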### Randomization and blinding

Among all nursing homes with similar conditions in the capital city of a province in China, three nursing homes will be selected to be included in this study by using the random number table [48], and then the envelope method will be used to determine which nursing home would implement which intervention. After obtaining the nursing homes’ consent to participate, the allocation will be kept concealed by random grouping. This work will be done independently by individuals who are not involved in the study and who keep a strict allocation sheet.

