**Methods:**

In this multicentre, single-blind, three-arm parallel randomized controlled study, we aim to enrol 78 older adults aged 65 years or older with a score of ≥ 11 on the Geriatric Depression Scale, and participants will be randomly assigned to either a reminiscence therapy group, a reminiscence therapy with memory specificity training group or a usual care group. Assessments will be conducted at baseline (T0) as well as immediately post-intervention (T1) and 1 (T2), 3 (T3) and 6 (T4) months post-intervention. The primary outcome measure is self-reported depressive symptoms, measured using the GDS. Secondary outcome measures include measures of autobiographical memory, rumination, and social engagement.

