### Study Design

A multicentre, single-blind, three-arm, randomized controlled trial will be conducted to assess the effect of reminiscence therapy combined with memory specificity training on improving autobiographical memory in older adults and further assess the effect on improving depressive symptoms in older adults. Based on the screening criteria, 78 participants will be recruited from three nursing homes in the provincial capital of China, and participants will be randomly divided into three groups in a 1:1:1 ratio. Participants in the first group will receive a 4-week intervention with reminiscence therapy, participants in the second group will receive a 4-week intervention with reminiscence therapy combined with memory specificity training, and participants in the third group will receive 4 weeks of usual care, followed by a 24-week follow-up.

Data will be collected at baseline, immediately postintervention, 1 month, 3 months, and 6 months postintervention. The study design is shown in Fig. 1. After the intervention, the same instructions will be given to a third group to ensure that more older adults benefit.

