### Participants

#### Eligibility and recruitment

Participants will be recruited from all three nursing homes simultaneously.

Once a nursing home has a sample of 26 subjects, they will proceed to the next step. Inclusion criteria are age ≥ 65 years; nursing home residence ≥ 3 months; Geriatric Depression Scale score ≥ 11; Mini-mental State Examination score ≥ 21; and voluntary participation in this study. Exclusion criteria include the acute onset of major illnesses such as cardiac, respiratory, digestive, or neoplastic disease; the development of a psychological illness other than depression; the taking of antidepressants or psychotropic drugs; an imminent discharge from a nursing home involved in the study; and receipt of other psychological treatment within the past 3 months.

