#### Reminiscence therapy

The group will implement group reminiscence therapy with 4 reminiscence phases. Each subgroup will consist of 1 implementer and 6–7 participants and will focus on 1 growth phase once a week for 90 min each time. The implementer will be responsible for guiding and encouraging the group members to freely recall past experiences and ensuring that each participant speaks for at least 10 min. The intervention details are shown in Table 2.

**Table 2 Tab2:** Intervention details

Sessions	Content
1st (week 1)	**Life stage**: Childhood (0–18 years) **Topic**: family, study experience, holidays etc. **Members**: 1 implementer and 6–7 participants. **Duration**:90 min. **Method**: The implementer will be responsible for guiding and encouraging the group members to freely recall past experiences and ensuring that each participant speaks for at least 10 min.
2nd (week 2)	**Life stage**: Young adulthood (18–25 years) **Topic**: friendship, education, technology change etc. **Members**: 1 implementer and 6–7 participants. **Duration**:90 min. **Method**: The implementer will be responsible for guiding and encouraging the group members to freely recall past experiences and ensuring that each participant speaks for at least 10 min.
3rd (week 3)	**Life stage**: Adulthood (25–65 years) **Topic**: spouse, parenting, professional experience etc. **Members**: 1 implementer and 6–7 participants. **Duration**:90 min. **Method**: The implementer will be responsible for guiding and encouraging the group members to freely recall past experiences and ensuring that each participant speaks for at least 10 min.
4th (week 4)	**Life stage**: Old age (over 65 years) **Topic**: philosophy of life Looking back etc. **Members**: 1 implementer and 6–7 participants. **Duration**:90 min **Method**: The implementer will be responsible for guiding and encouraging the group members to freely recall past experiences and ensuring that each participant speaks for at least 10 min.

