### Quality Control

Our study team is an experienced group consisting of a senior expert in the field of geriatric care, three graduate students specializing in geriatric care, and nursing home professional nurses. Experienced nursing home professional nurses and the researcher on the team will be responsible for recruiting participants. Participants who meet the inclusion criteria will be screened, informed of the study details by the researcher, and asked to sign a consent form if they agree to participate. If there are complex clinical issues, our researchers, nursing specialists, and nursing home professional nurses will work together to find solutions.

The investigators will provide uniform and standardized training to all personnel implementing the intervention, and will conduct group training and related assessments on the use of the scale to ensure that implementers are familiar with the content and master the use of the scale, and that it will be tested and collected on the spot to ensure the validity and recall of the questionnaire.

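### The protocol describes two incompatible units of allocation; if whole nursing homes are allocated, as the randomisation section says, arm and home are fully confounded

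*Protocol article*

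**What the plan says.** The abstract says that "participants will be randomly assigned to either a reminiscence therapy group" or to one of the other two arms, and Study Design says that "participants will be randomly divided into three groups in a 1:1:1 ratio". Both make the resident the unit of randomisation.

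Randomization and blinding describes something else. From homes with similar conditions in one city, "three nursing homes will be selected to be included in this study by using the random number table", and "then the envelope method will be used to determine which nursing home would implement which intervention". The section then says that allocation is concealed once the homes have agreed to take part, and that people outside the study do this work. It describes no step that randomises residents within a home.

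Two other sections bear on the question. Eligibility and recruitment says: "Once a nursing home has a sample of 26 subjects, they will proceed to the next step". Reminiscence therapy says: "Each subgroup will consist of 1 implementer and 6–7 participants". Under Quality Control, "Experienced nursing home professional nurses and the researcher on the team will be responsible for recruiting participants".

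Statistical analysis plans repeated-measures ANOVA, or Kruskal–Wallis for skewed data, on individual scores and mentions no home term. The limitations in the Discussion cover the small sample and generalisability from three homes, consistency of implementation across team members, and self-report bias. They do not mention that home and arm may coincide.

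**The concern.** The unit of allocation decides what the trial can conclude, and the article states it in two incompatible ways. If residents are randomised within homes, each home contributes to every arm and differences between homes can be removed. If each home is given whole to one intervention, every difference between homes (staff, case mix, local routine, implementer, events during follow-up) is also a difference between arms. The stated aim is to confirm effectiveness, and a comparison of three homes with one per arm cannot do that, however many residents each home supplies.

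There is a second, conditional risk. Home nurses help to recruit, and the article does not say whether a home's allocation is known before its residents are enrolled. If it is, knowledge of the arm could influence who is approached and who agrees.

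**Working it through.** **1. Which reading do the numbers fit?**
- Sample size calculation: 24 per group with 10% dropout. 24 × 1.1 = 26.4, taken as 26, and 26 × 3 = 78, the stated total.
- Eligibility and recruitment: 26 per home, and 26 × 3 homes = 78. The size of a home's sample equals the size of an arm.
- Reminiscence therapy: subgroups of 6–7. 26 / 4 = 6.5, so one arm of 26 makes four subgroups (6 + 6 + 7 + 7 = 26). With residents randomised within homes, each home would hold 26 / 3 ≈ 8.7, that is 8 or 9 per arm, which does not divide into subgroups of 6–7.

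Both figures fit one home per arm. They do not prove it, because 26 per home is also possible with randomisation within homes.

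**2. What follows if homes are allocated?**
- Homes: 3. Arms: 3. Homes per arm: 1.
- Degrees of freedom for between-home variation within arm: 3 − 3 = 0.

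A home term would be collinear with arm. Between-home variance cannot be estimated from the trial's own data, and adding residents does not help because the home component does not shrink with cluster size. Adjusting for baseline scores removes only measured differences between residents.

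**3. Illustration of size: post-intervention scores.** The article gives no intracluster correlation (ICC). Values of 0.01, 0.05 and 0.10 are assumed here. The number analysed per home is m = 24, from the sample size section. With one home per arm, the variance of an individual-level test statistic is inflated by

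k = 1 + m × ICC / (1 − ICC),

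and the true type I error of a nominal two-sided 5% pairwise test is 2 × [1 − Φ(1.96 / √k)].

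| Assumed ICC | k | 1.96 / √k | True type I error |
|---|---|---|---|
| 0.01 | 1.242 | 1.758 | 7.9% |
| 0.05 | 2.263 | 1.303 | 19.3% |
| 0.10 | 3.667 | 1.024 | 30.6% |

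Using the t distribution with 46 degrees of freedom instead gives 7.7%, 18.7% and 29.9%, so the approximation makes little difference.

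**4. The planned contrast is different.** The Geriatric Depression Scale is measured at T0 and at four later times. In a group-by-time contrast, a home effect that is the same at every visit cancels. A simulation with ICC 0.10, 24 per home, one home per arm and a home effect constant over time rejected about 30% of the time for post-intervention scores and about 5% for change from T0. The table therefore does not describe the group-by-time test. That test is biased by any home-level difference in change over the 4 weeks of intervention and 24 weeks of follow-up. The document gives no figure for such differences, and with one home per arm the trial cannot estimate them.

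**The case against.** The strongest reply is that the home-level reading is not settled. The abstract and Study Design both state participant-level randomisation, and if they govern, the confounding disappears. That is correct, and it is why the firm finding is the contradiction and the confounding is conditional. But the mechanism is described only once, at home level, so under either reading some text is wrong.

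The plan also has partial mitigations: homes with similar conditions, uniform training of implementers, and a baseline measurement. These reduce some differences between homes. They do not make the home effect zero or estimable.

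Three stronger readings are tempting, and the documents do not support them.
- A reader might infer that homes learn their arm before residents are enrolled. The article gives no timing for the envelopes relative to enrolment, and it claims concealment. Selective enrolment is an open risk, not an established fact.
- A reader might infer that the homes start at different calendar times because each proceeds on reaching 26. The same section says that recruitment is simultaneous in all three homes, and the next step is not defined. Staggered starts are possible, not stated.
- A reader might take 19% or 31% as the error rate of the planned repeated-measures analysis. Those figures apply to post-intervention scores under assumed ICCs.

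**Conclusion.** The point stands in this form. The article contradicts itself on the unit of allocation, and the passages must be reconciled. If the randomisation section governs, arm and home coincide, there are no degrees of freedom for between-home variation within arm, and the individual-level tests cannot support a confirmatory causal claim. The limitations do not disclose this.

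The structural conclusion needs no assumed figure. The illustrative type I error of about 8%, 19% and 31% rests on assumed ICCs, 24 analysed per home and a pairwise comparison of post-intervention scores. For the group-by-time contrast no figure can be given; the bias equals whatever home-level difference in change exists. This must be resolved, because the trial's main claim depends on it.

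**What to change.** Choose one of two routes.

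**(a) If participant randomisation is intended and enrolment has not begun.** Rewrite Randomization and blinding so that residents are randomised within each home after consent and T0, stratified by home. Allocation of 9/9/8, 9/8/9 and 8/9/9 over the three homes gives 26 per arm with the same 78 residents. Put home in the model as a fixed effect. This has real costs. Reminiscence therapy with and without memory specificity training differ only in the prompts, so housing both in one home risks contaminating the key contrast. Each home must also host all three arms. The 8–9 residents per arm per home must be reconciled with the stated subgroups of 6–7: kept as one group, the minimum of 10 minutes' speaking each takes 80–90 of the 90 minutes; split in two, the groups hold 4–5.

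**(b) If home-level allocation is kept, or enrolment has begun** (the article does not give recruitment status). Replace the statements of participant-level 1:1:1 randomisation in the abstract and Study Design with an accurate description of one home per arm. State the home-arm confounding as a limitation. Report estimates without confirmatory p-values or causal claims. Where still possible, reveal the allocation only after recruitment and T0 are complete in all three homes. This needs no further residents; the cost is a weaker claim.
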